# Frailty Prevention Care Management Program (FPCMP) on Frailty and Health Function in Community-Dwelling Older Adults: A Quasi-Experimental Trial Protocol

**DOI:** 10.3390/healthcare11243188

**Published:** 2023-12-17

**Keywords:** frailty, prevention care management, Total Resistance Exercises, senior fitness test, nutrition assessment

## Abstract

Background: Frailty often results from deteriorating muscle strength and decreased physical function in older adults. Frailty includes not only physical components, but also psychological and social aspects. Previous research has shown that exercise programs, especially resistance exercises combined with nutritional care, can reduce frailty. Objectives: This study aimed to develop a Frailty Prevention Care Management Program that prevents frailty and improves physical activity and nutrition compared to usual care for community-dwelling older adults. Methods: A quasi-experimental and single-blinded trial with a non-equivalent control group using a before-after design will be performed involving Frailty Prevention Care Management Program interventions, taking place both at the communities. Participants will be divided into two different intervention groups and two control groups. All groups will be assessed three times: at baseline, immediately after the intervention, and 3 months post intervention. A total of 72 community-dwelling older adults are recruited. This intervention includes an exercise program (design TRX program) and nutritional education. The control group will not receive any specific exercise training. The primary outcome shall comprise the effect of the Frailty Prevention Care Management Program on frailty using the Taiwanese version of the Tilburg frailty indicator. Secondary outcomes include the effect of physical activity using the Senior Fitness Test and nutrition measures using the Mini Nutritional Assessment-Short Form. A generalized estimating equation is constructed to analyze the effects of the intervention. Conclusions: This trial will provide vital information to guide interventions to improve outcomes (frailty, physical activity, and nutrition) and inform the integration of nutrition and TRX exercises in community-dwelling older adults.

## 1. Introduction

According to a systematic and meta-analysis research involving data from more than 120,000 older adults from 28 countries, the pre-frailty incidence rate per 1000 person-years for people over 60 years old was 43.4, and the frailty incidence rate was 150.6 [1]. As older adults grow older, frailty problems also appear, resulting in decreased daily activities, decreased muscle strength, a poor sense of balance, chronic diseases, and other unhealthy conditions, aggravating the pre-frailty of older adults and leading to hospitalization, falls, and death [2].

Frailty reduces the quality of life in older adults [3]. Fried et al. (2001) identified the symptoms of frailty as follows: weight loss, fatigue, low grip strength, slow gait, and low physical activity [4]. Frailty was defined as the presence of at least three of these symptoms. Frailty is usually caused by the deterioration of muscle strength and decline in physical function, often due to a lack of physical activity, chronic nutritional deficiencies, depression, or inadequate support systems [5]. The concept of frailty includes not only physical components, but also psychological and social aspects [6]. Brown et al. (1995) proposed that vulnerability is a multidimensional theoretical framework with common influencing factors. This cluster includes physical, cognitive/psychological, socioeconomic, nutritional, and social factors, as well as disease and aging, reflecting a bio-psycho-social-spiritual view of health [7]. Many researchers have indicated that frailty is multidimensional and that its definition should comprise nutrition, cognition, mentality, ADL, and other aspects. Therefore, using this protocol, we aim to adopt findings and assessment tools (Tilburg frailty indicator (TFI)) from previous studies, using the multi-dimensional perspective of frailty. In addition, some research studies have found that physical frailty and social frailty are related. A higher prevalence of muscle weakness and loss of skeletal muscle mass in participants with social frailty was shown than in those without [8]. As suggested by Cook et al. (2017), due to the multidimensional nature of frailty, the combination of physical, psychological, and social frailty is more likely to contribute to disability and mortality than physical, psychological, or social frailty alone [9]. To summarize the above, uncovering the potential pathways of frailty in combination with its three domains (physiological, psychological, and social levels) is essential and could increase our understanding of frailty from a more comprehensive perspective.

The symptoms of frailty mentioned above are also easily observed in the lives of older adults in the community. Intervention to prevent or delay frailty has important benefits for older adults. If the early stage of frailty can be detected and intervention measures can be taken in the early stage, this can delay or prevent frailty from causing adverse health effects. Intervention to prevent or delay frailty has essential benefits for older people, health services, and the current government focus on long-term care.

Much research has been conducted on nutrition, physical activity, exercise, social support, and multiple interventions to prevent frailty [10,11]. One study showed that taking a twice-daily oral supplement rich in energy, protein, fiber, vitamin D, and calcium effectively enhanced physical performance when combined with an exercise program. Exercise programs, particularly resistance exercises combined with nutritional care, can reduce frailty in primary care settings [12,13]. Another randomized controlled study on nutritional support and physical training in frail and pre-frail patients showed that combining these interventions effectively enhanced strength and physical performance [14,15].

Exercise interventions appear to be essential components of multidomain interventions. This program combines strength, resistance (aerobic), balance, and flexibility training. It has been shown to significantly improve functional capacity, which is the key to maintaining independence from tools of daily living and essential activities [16]. The characteristics of an exercise program (i.e., frequency, intensity, duration, and type of training) affect its effectiveness [13]. To better understand this issue, exercise interventions reported in the literature were analyzed using the American Institute of Physical Education’s Frequency, Intensity, Time, Type, Volume, Progression (FITT-VP) framework [17].

Based on recent research and the World Health Organization’s 2020 guidelines on physical activity and sedentary behavior, multi-component physical activity may reduce the risk of fall-related injuries in older adults, suggesting that they should include it in their weekly physical activity. They should engage in moderate- or higher intensity multi-component physical activity on 3 or more days per week to enhance functional capacity [18], 30–45 min at a time, for at least 5 months [19]. Studies have also confirmed that physical activity, especially enhancing muscular strength, balance, flexibility, and muscular endurance, is an effective treatment for frailty [20]. Daily activities and functional training are becoming increasingly important in older adults.

Total Resistance Exercises (TRX) are a core stability training program. This training mode combines physical function and strength. Body strength and balance sensitivity training can be performed [21]. Previous studies have found that TRX training can be used for trunk muscles, such as the transverse abdominis, internal oblique, rectus abdominis, multifidus, and vertical spine muscles [22,23]; it builds strong muscles by burning fat located on the muscle, strengthens the chest muscles and legs, and increases flexibility and endurance [24]. Thus, TRX training appears to provide greater benefits than traditional resistance training. Consider the following advantages of using TRX as a health function for training older adults: practicality, simplicity, ease of use, and small footprint for performing various exercises [25]. Aslani et al. (2018) found that after five weeks of training, increasing the strength of the lower body muscles and increasing the activity of the core stabilizer muscles through TRX training improved the balance performance of the subjects [26]. Exercise can effectively prevent or delay frailty and maintain physical function. Gaedtke and Morat conducted a 12-week training program on 11 old adults and concluded that strength and balance were significantly increased [21]. For older adults with total knee replacement, a six-week sling training led to significant quadriceps and hamstring strength improvements of 77% and 56%, respectively [27]. In addition, applying group-directed intervention was the choice for the delivery of our present multi-domain intervention. This is because it is known to promote social participation, physical activity, psychological factors, and social relationships [21].

However, there is still a lack of knowledge about the effects of sling training in frail older adults. Indeed, so far, there are no published studies on TRX exercise combined with a nutrition program in frailty older adults. Therefore, this study aimed to develop a Frailty Prevention Care Management Program that prevents frailty and improves physical activity and nutrition compared to usual care for community-dwelling older adults. It has three objectives:(1)To develop and implement a program for the Frailty Prevention Care Management Program of community-dwelling older adults;(2)To assess the impact of the intervention regarding frailty (physical, psychologic, and social domain), health function, and nutrition in the two groups (experimental and control group);(3)To assess the impact of the Frailty Prevention Care Management Program intervention regarding frailty (physical, psychologic, and social domain) and nutrition immediately post-intervention and 3 months post intervention in the two groups.

## 2. Materials and Methods

This quasi-experimental and single-blinded trial with a non-equivalent control group uses a before-after design. The FPCMP-Old Age program trial will take the form of a non-randomized, two-group (experimental and control group) trial, with repeated measures at three time-points to improve the community effects of different levels of frailty, health function, and nutrition (Table 1). Cluster RCTs are increasingly used, particularly in primary care research [28], in which groups of participants rather than individual participants are randomized. However, practical challenges remain, such as an increased sample size and complex recruitment procedures. Due to time and resource limitations, this study did not choose to use cluster RCT at the level of communities.

When collecting research samples, the “community” was deliberately used as the unit of collection. Considering that this study recruits four units (including the experimental group and the control group), community units need to be involved. The experimental group and the control group cannot be recruited from the same unit, and this study is prone to contamination problems. Another reason why this study cannot use random assignment is to consider the four community units that received the case. If random assignment is used, there is a chance that strongholds with better or worse functionality will be assigned to the same group (experimental group or control group). Therefore, this study adopts a match to make the health attributes of the two groups of participants close. It was expected that the proportion of control confounding factor allocation will be balanced within the two groups. Therefore, to control or reduce the impact of confounding factors on research, the community was selected, and the experimental and control groups will be recruited from four different communities, but with similar health attributes (Chiayi and Yunlin County).

### 2.1. Participants and Eligibility

The scope of this study was to accept cases in Chiayi and Yunlin County. Four convenient samples, two experimental groups, and two control groups of people meeting the inclusion criteria will be drawn from four communities, respectively. These four communities are similar in the main aspects, such as population density, economics, and level of community health services. With the support of the local health bureau, the program was accepted by the communities. The research nurses independently completed the data collection, and data collection was completed through one-on-one interviews.

The participants could not be masked after allocation because of the nature of the intervention. The research nurses were similarly not masked because they had to allocate patients to the experimental group and monitor the integrity of the intervention. This study blinded the athletic trainers and did not know that which community participants were the experimental group, because athletic trainers had no role in recruitment, outcome assessment, or data analysis for this study.

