This study has several limitations. First, quasi-experimental studies’ lack of randomization may lead to selection bias. The main consideration is that communities willing to participate must obtain the consent of all older adults to participate in the program. In addition, the random sampling method is likely to cause dissatisfaction among the older adults in the community, because most older adults hope to participate in this project together. The sample was not randomized for pragmatic and ethical reasons, as it might be considered unethical not to prescribe exercise to frail older adults [53]. However, the lack of randomization resulted in the results being contaminated with confounding variables. Second, a potential limitation of this study is that participants and research nurses could not be blinded, as it would be impossible to blind them in non-drug trials. Therefore, performance bias may be unavoidable. In addition, to obtain the consent of all participants in the experimental group, participants must be informed of the risks of participating in the study. In this case, the “Hawthorne effect” may occur in the experimental group.

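### The trial is labelled single-blinded, but the only party called blind has no part in outcome assessment; the interview-based primary outcome is collected unblinded and detection bias is not named

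*Protocol article*

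**What the plan says.** The Abstract and section 2 (Materials and Methods) give the same label; section 2 reads "This quasi-experimental and single-blinded trial with a non-equivalent control group uses a before-after design".

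Section 2.1 (Participants and Eligibility) then describes each party:

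- Participants: "The participants could not be masked after allocation because of the nature of the intervention".
- Research nurses: "The research nurses were similarly not masked because they had to allocate patients to the experimental group and monitor the integrity of the intervention". On their other task: "The research nurses independently completed the data collection", through one-on-one interviews.
- Athletic trainers: "This study blinded the athletic trainers and did not know that which community participants were the experimental group". The reason given is that they take no part in recruitment, outcome assessment or data analysis.

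The limitations in section 6 (Discussion) concede that "participants and research nurses could not be blinded" and conclude that performance bias may be unavoidable. They also mention a Hawthorne effect in the experimental group.

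Section 3.1.2 makes the TFI-T the primary outcome: 15 items scored 0 or 1, total 0 to 15, covering physical, mental and social frailty.

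**The concern.** Readers usually take single-blinded to mean that either the participants or the outcome assessors do not know the group. Section 2.1 rules out both. The label then rests on a third party whose blindness, even if it were real, could not affect how any outcome is measured.

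This matters most for the TFI-T. Its items include fatigue, anxiety, coping and social support. The answers come from people who know whether they attended the programme, and are elicited by interviewers who know it too and who also monitor the programme's integrity. Expectation on either side can move the score without any change in frailty. The trial is already non-randomised, so a stated safeguard that does not exist should not be left in the design description.

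**Working it through.** The core of this point is a comparison of statements and needs no arithmetic. The article gives no figure for assessment bias, so there is none to reproduce.

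**Step 1. Who is blind, and does it bear on measurement?**

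| Party | Role in the article | Masked? | Could masking protect the outcomes? |
|---|---|---|---|
| Participants | Answer the TFI-T | No (2.1, 6) | Yes, but absent |
| Research nurses | Allocation, monitoring, data collection by interview | No (2.1, 6) | Yes, but absent |
| Athletic trainers | No recruitment, assessment or analysis role | Said to be (2.1) | No, since they measure nothing |
| Data analysts | Masking not described | Not stated | No claim is made |

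No row combines a stated masking with a role in measuring outcomes.

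**Step 2. Is the trainers' blindness credible?** Section 4.3 says controls receive no specific exercise training. The Discussion's subsection on development challenges says athletic trainers need TRX training and that trained coaches guide participants at a ratio of 1:5. If the trainers are those coaches, every class they lead is an experimental class and they know it. If they are not, their blindness still has no bearing on measurement. The label fails either way.

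**Step 3. Which bias follows?** Unmasked interviewers create detection bias. Unmasked respondents create reporting bias on self-reported items. Performance bias, which section 6 names, concerns differences in care or behaviour between groups. The Hawthorne remark comes close to the participants' side but does not cover the interviewers.

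**Step 4. Illustration of scale (assumed shifts).** Take a two-sided 5% two-sample t-test, no true effect, and a systematic assessment shift of d SD between arms. The rejection probability is P(|T| > t critical), where T is non-central t with 2n − 2 degrees of freedom and non-centrality d × √(n/2). The values of n come from section 5.2: 36 recruited per group, 30 needed.

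| Assumed shift d | n = 36: non-centrality | Rejection | n = 30: non-centrality | Rejection |
|---|---|---|---|---|
| 0 | 0 | 5% | 0 | 5% |
| 0.2 | 0.2 × √18 = 0.85 | 13.3% | 0.2 × √15 = 0.77 | 11.9% |
| 0.3 | 0.3 × √18 = 1.27 | 24.1% | 0.3 × √15 = 1.16 | 20.8% |

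For comparison, the effect detectable with 80% power under the same test is 0.67 SD at n = 36 and 0.74 SD at n = 30. A 0.2 SD shift is thus 0.2/0.67 = 30% or 0.2/0.74 = 27% of it. Section 5.2 states no effect size, so 0.67 and 0.74 are back-calculated. The planned analysis is a GEE over three time points, so the t-test shows only an order of size.

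**The case against.** **The facts are disclosed.** This is the strongest objection, and it largely stands. Section 2.1 says plainly that participants and nurses were unmasked, and section 6 repeats it beside selection bias, confounding, performance bias and a Hawthorne effect. A reader might infer that the article conceals its unblinded assessment; it does not. What remains is a label in the Abstract and section 2 that its own methods text does not support, and one unnamed bias.

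**The nurses' allocation role.** It is tempting to read section 2.1 as nurses choosing individuals for an arm, in conflict with assignment by community. The documents do not support that. Sections 2 and 2.1 draw two experimental and two control samples from four separate communities, so group follows community. The phrase about allocating patients is more plausibly loose wording than a second allocation mechanism, and needs only rewording.

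**Inferred links.** Section 2.1 does not say that the trainers deliver TRX; the Discussion makes it likely. No passage says who runs the Senior Fitness Test, so the point should not be extended to those tests as established fact. Neither gap affects the conclusion on the TFI-T interviews.

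**A change of rota would cure it.** It would not. With only four communities and unmasked participants, a nurse moved to another community would know or soon learn its group. It would also come too late for T1: section 4.2.1 schedules the course to the end of September 2023, T1 is the following week, and the article is dated 17 December 2023. The number of nurses is not given, so feasibility cannot be judged.

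**The figures prove a biased result.** They do not. The 0.2 and 0.3 SD shifts have no source in the documents.

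**Conclusion.** The point holds as a misstatement of a design property. On the article's own description, neither those who answer the TFI-T nor the nurses who collect the data are masked, and the one party called blind has no role in measurement. The trial is open-label for its primary outcome, and detection bias belongs among the limitations.

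This rests on one modest inference: that the nurses who complete the data collection by interview administer the TFI-T. No other interviewer is named. It does not depend on whether the trainers coach TRX, on who runs the fitness tests, or on any assumed size of bias. The size is unknown; the rates of 13% and 24% with 36 per arm only show that a modest assumed shift would be enough to matter.

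**What to change.** 1. In the Abstract and section 2, replace single-blinded with open-label.
2. In section 2.1, delete the sentence on blinding the athletic trainers.
3. In section 2.1, reword the sentence on the nurses so that group follows community and no individual allocation by nurses is implied.
4. In the section 6 limitations, add that the TFI-T effect is open to detection bias from unmasked interviewers and to reporting bias from unmasked participants, and must be interpreted accordingly.

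These are text edits and cost almost nothing. They change no procedure and no analysis.

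Optionally, for assessments still to be done and if existing nurses allow it, let interviews be done by nurses who did not recruit or monitor in that community. This separates roles and may reduce expectation effects. It should be reported as such and not as blinding. Its cost depends on nurse numbers and travel, which the article does not give.

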#### 2.1.1. Establish a Cooperative Relationship with the Local Township Head, Village Head, or Person in Charge of the Base

We invited the township head, section chief of the township office, village head, or person in charge of the community to discuss the purpose of this research. The communities were positive and pleased to collaborate with our program. Further, we explained the content of the activities, the participants, and procedures of accepting cases, among others, to obtain the support of relevant units in the community and establish a cooperative relationship.

#### 2.1.2. Preliminary Solicitation of Patients Willing to Participate in the Testing

After the invitation process, the information sheets will be distributed and explained. Those individuals who agree to participate will be requested to provide written informed consent, and subsequently, they will be further screened to identify their eligibility to participate. Through questionnaires, case capital data, frailty status, physical function, nutrition, and other tools for older adults in the community were collected. Primary and secondary study outcomes will be collected for the intervention and control groups at baseline assessment (T0), the week immediately post intervention (T1), and at 3 months post intervention (T2; See Figure 1).

The study protocol was approved by the regional Chang Gung Medical Foundation 202202269B0 (See Supplementary File S1). The study protocolwas registered in the ClinicalTrial.gov-register (NCT05883423).

